### Sample size calculation

Our sample size is based on the primary outcomes of hepatic injury and liver fat. For hepatic injury, we used pilot data from our lab to determine that a sample size of *n* = 19 in each group would have 80 % power to detect a difference in liver stiffness of 4.1 kPa with FibroScan assuming a standard deviation of 4.0 kPa and a 0.025 two-sided significance level. For the Fibrotest [109], a sample size of *n* = 10 per group would have 80 % power to detect a difference in Fibrotest score (0.0 to 1.0) of 0.08 assuming a standard deviation of 0.056 and a 0.025 two-sided significance level. For liver fat measured by MRI [110], a sample size of *n* = 25 per group will have 80 % power to detect a difference in hepatic fat of 4.4 % assuming a standard deviation of 5.0 % and a 0.025 two-sided significance level. Based on these calculations, we will enroll *n* = 25 per group. Assuming a dropout rate similar to that in our previous prebiotic trial [72] of approximately 20 %, we will recruit a total of 60 participants (*n* = 30 per group).

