### Statistical analyses

Statistical analyses will be performed using SPSS 22.0 software (IBM, Armonk, NY). Values with skewed distribution will be logarithmically transformed prior to analysis. Baseline characteristics will be compared between groups using chi-square for categorical variables and t-tests for continuous variables. Primary analysis will be performed on an intent-to-treat basis, regardless of subject compliance. The primary outcome measures are change from baseline to 24 weeks in hepatic injury (Fibrotest, FibroScan) and liver fat (percent measured by MRI). ANCOVA, with testing for confounding factors (sex) and potential covariates (BMI, age and fasting insulin) will be used to assess the difference between groups at weeks 0 and 24. Should the main effect of diet be significant, Tukey’s multiple comparison test will be used. Secondary outcomes measured at 0 to 24 weeks (e.g. satiety hormones, body fat, glycemia and insulinemia) will be analyzed with ANCOVA as above. For variables measured over time (e.g. body weight, satiety hormones and glucose at 0, 30, 60, 120 and 180 minutes), a mixed model of repeated measures ANCOVA will be applied to examine the effect of treatment, time and their interaction. Our planned secondary analysis will be per protocol with all participants who complete the 24 week intervention and are compliant based on consumption of ≥80 % the product doses. Cases with missing outcome data will be excluded from analysis. Results will be considered statistically significant (2-sided) at *P* ≤ 0.025 (Bonferroni adjustment for 2 primary outcomes).

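### Holm's step-down test would be a cheap gain over the planned flat Bonferroni rule for the two primary outcomes, provided hepatic injury first contributes a single p-value

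*Protocol article*

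**What the plan says.** The Statistical analyses section of the protocol article names the primary measures: "The primary outcome measures are change from baseline to 24 weeks in hepatic injury (Fibrotest, FibroScan) and liver fat (percent measured by MRI". It closes with the decision rule: "Results will be considered statistically significant (2-sided) at *P* ≤ 0.025 (Bonferroni adjustment for 2 primary outcomes". It describes no step-down, gatekeeping or reuse of unspent alpha.

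The Sample size calculation section uses the same level for each measure:

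- **MRI liver fat:** 25 per group to "detect a difference in hepatic fat of 4.4 % assuming a standard deviation of 5.0 % and a 0.025 two-sided significance level".
- **FibroScan:** 19 per group for a "difference in liver stiffness of 4.1 kPa with FibroScan assuming a standard deviation of 4.0 kPa and a 0.025 two-sided significance level".
- **FibroTest:** 10 per group for "a difference in Fibrotest score (0.0 to 1.0) of 0.08 assuming a standard deviation of 0.056", at the same level.

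It concludes: "Based on these calculations, we will enroll *n* = 25 per group". It then allows for about 20% dropout by recruiting 30 per group. Sizing and testing therefore agree on 0.025. The plan counts two outcomes, but hepatic injury is carried by two measures.

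**The concern.** Under the planned rule each outcome must reach 0.025 whatever the other one shows. Suppose hepatic injury is clearly significant and liver fat gives p = 0.03. The plan calls liver fat negative, although a 5% family-wise limit over two outcomes does not require that.

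Holm's procedure tests the smaller p-value at 0.025, exactly as planned. Only if that is significant does it test the larger at 0.05. It controls the family-wise error under any correlation between the outcomes.

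MRI liver fat stands to gain most. It sets the sample size and has the least power of the three measures, so a p-value between 0.025 and 0.05 is a realistic result for it.

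**Working it through.** **Inputs.** From the Sample size calculation section, as difference divided by standard deviation:

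- MRI: 4.4/5.0 = 0.88
- FibroScan: 4.1/4.0 = 1.025
- FibroTest: 0.08/0.056 = 1.43

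The number analysed per arm is 25 as stated, or 30 × 0.8 = 24 after the assumed dropout. The correlation between outcomes is not given. I take 0 and show the effect of varying it.

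**Reproducing the plan.** Use n = 2(z₀.₉₈₇₅ + z₀.₈₀)²/d², with z = 2.241 and 0.842:

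- FibroScan: 18.1, so 19
- FibroTest: 9.3, so 10
- MRI: 24.5, so 25

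All three match. The t-distribution needs one more per group each time (20, 11 and 26), so MRI power at 25 is 78.5% by t-test.

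**Single-test power (non-central t).**

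| n per arm | MRI at 0.025 (m₁) | MRI at 0.05 (m₂) | FibroScan at 0.025 (f₁) | FibroScan at 0.05 (f₂) |
|---|---|---|---|---|
| 24 | 0.7652 | 0.8471 | 0.8871 | 0.9352 |
| 25 | 0.7846 | 0.8618 | 0.9009 | 0.9441 |

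**Bonferroni against Holm, independent outcomes.**

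MRI under Holm = m₁ + (m₂ − m₁)f₁:

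- n = 24: 0.7652 + 0.0819 × 0.8871 = 0.838, a gain of 7.3 points
- n = 25: 0.7846 + 0.0772 × 0.9009 = 0.854, a gain of 7.0 points

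Both under Bonferroni = m₁f₁. Both under Holm = m₂f₂ − (m₂ − m₁)(f₂ − f₁):

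- n = 24: 0.679 against 0.788, a gain of 10.9 points
- n = 25: 0.707 against 0.810, a gain of 10.3 points

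At least one win = 1 − (1 − m₁)(1 − f₁): 97.3% at 24 and 97.9% at 25, the same under either rule.

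**How far the gains move.**

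- *Correlation* (simulation, n = 25): at 0.3, 0.5 and 0.8 the MRI gain is 6.8, 6.5 and 6.2 points. The gain for both is 9.5, 8.9 and 7.5.
- *FibroTest alone carries hepatic injury* (power 99.6% at n = 25): MRI +7.7, both +7.9. At n = 24: MRI +8.1, both +8.4.
- *FibroTest and FibroScan must both be significant* (n = 25): MRI +6.9, both outcomes +10.4.
- *FibroScan effect half that planned* (n = 24): f₁ falls to 0.30, so the MRI gain is 0.0819 × 0.30 = 2.5 points.
- *FibroScan effect a quarter of that planned* (n = 24): about 0.7 points.
- *No FibroScan effect* (n = 24): 0.0819 × 0.025 = 0.2 points.

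**If three p-values are tested.** Three measures, each at a flat 0.025, give 1 − 0.975³ = 7.3% family-wise error under independence and at most 7.5%. Three-test Holm starts at 0.05/3 = 0.0167. At n = 24 with independent measures, MRI power compared with 76.5% under the flat 0.025 is:

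- about 71% if only liver fat responds
- about 76% if liver fat and FibroScan respond but FibroTest does not
- about 84% if all three respond as planned

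**The case against.** The strongest reply is that nothing here is wrong. The plan pre-specifies a valid 5% procedure and sizes the trial for it, so Holm adds power beyond what the sponsor set out to buy. That stands, and it is why the point is an improvement and not an error.

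Three further objections also stand:

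- **The gain is conditional.** The FibroScan difference comes from the investigators' own pilot data. If it is optimistic, most of the MRI gain disappears.
- **A joint win is not a success criterion.** The plan does not ask for both outcomes to be significant, so the 10-to-11-point figure describes a useful result and not the plan's own target.
- **Single-step testing has a benefit.** Each outcome has a fixed threshold and a matching simultaneous interval. Under Holm, a liver-fat win with p between 0.025 and 0.05 would sit beside a Bonferroni interval that includes zero.

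A reader might also infer that Holm can never do worse than the current plan, however many primary p-values are tested. The documents do not support that. They name three measures under an adjustment for two. If all three enter the procedure, its first step is stricter than 0.025, and liver-fat power can fall. That loss is the price of the larger family and not of Holm itself. With three tests the fair comparison is Holm against Bonferroni at 0.0167, because the flat 0.025 does not then hold 5%.

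**Conclusion.** The point holds as a cheap improvement. For two primary p-values, Holm rejects everything the planned rule rejects, at the same 5% family-wise error.

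If the planned effects are real and FibroScan carries hepatic injury, the gain is about 7 points for MRI liver fat. For winning on both it is 10 to 11 points with independent outcomes and 7.5 with correlation 0.8. If FibroTest alone carries hepatic injury, the gain for both is about 8 points. If hepatic injury does not respond, Holm gains almost nothing and costs no power.

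It would be too strong to say that the plan is invalid, that the trial loses 7 points unconditionally, or that the result holds for any family size. The rule is valid for two tests, the gain depends on the hepatic-injury effect, and the dominance over the current 0.025 holds only for two p-values.

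**What to change.** In the Statistical analyses section, for the primary outcomes only:

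1. State that hepatic injury contributes one p-value, either from one measure named in advance or by requiring both FibroTest and FibroScan to be significant (the larger of their two p-values). MRI liver fat contributes the other.
2. Test the smaller of the two at two-sided 0.025. Only if it is significant, test the larger at 0.05.

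If the sponsor prefers three p-values, the steps are 0.0167, 0.025 and 0.05, and the power should be restated, since liver-fat power may then fall below that of the current rule.

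The change is a few lines of text before unblinding, with no added patients, visits or data. The cost is the loss of an equally simple simultaneous confidence interval. Bonferroni-level intervals can still be reported, with a note that they may include zero for an outcome declared significant at the second step.

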### Primary outcome

#### Hepatic injury and liver fat

The primary outcome is change in hepatic injury and liver fat from baseline to 24 weeks. Improvement in liver injury will be defined by reduction in non-invasive and biochemical markers of fibrosis and inflammation. Fibrosis will be measured at baseline and 24 weeks using transient elastography (FibroScan), which has a high sensitivity for diagnosis and prognostic stratification of varying degrees of liver fibrosis [86, 87] and the Fibrotest which is a composite of serological markers and age and sex, that provides a quantitative estimate of liver damage (age, sex, gamma-glutamyl transpeptidase, bilirubin, α2-macroglobulin, haptoglobin, and apo-lipoprotein A1) [88]. The newer XL probe, specifically designed for obese patients, will be used for FibroScan [86]. Magnetic resonance imaging (MRI) will be performed at baseline and 24 weeks on a 1.5 T scanner (GE Medical Systems, Milwaukee, USA) to assess change in liver fat. MRI can detect fat in microscopic quantities and with chemical shift imaging (CSI) has a sensitivity of 90 % and specificity of 91 % [89]. Although costly, MRI is a front-runner in imaging modalities to quantify hepatic steatosis and represents an acceptable alternative to invasive liver biopsy. While still the gold standard in histological assessment of NAFLD, biopsy is not without risk and is limited by its lack of representation of the liver as a whole [90].

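### Three primary measures are each tested at 0.025, but the Bonferroni divisor counts two outcomes and no rule joins FibroScan and Fibrotest

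*Protocol article*

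**What the plan says.** The Statistical analyses section lists the primary measures as "change from baseline to 24 weeks in hepatic injury (Fibrotest, FibroScan) and liver fat (percent measured by MRI"). That is three measures under two labels. The same section sets the two-sided significance threshold at P ≤ 0.025 and explains it as a "Bonferroni adjustment for 2 primary outcomes".

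The Sample size calculation section treats all three as tests in their own right, each with 80% power:

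- FibroScan, 19 per group: "difference in liver stiffness of 4.1 kPa with FibroScan assuming a standard deviation of 4.0 kPa and a 0.025 two-sided significance level".
- Fibrotest, 10 per group: "difference in Fibrotest score (0.0 to 1.0) of 0.08 assuming a standard deviation of 0.056 and a 0.025 two-sided significance level".
- MRI liver fat, 25 per group: a difference of 4.4% with SD 5.0%, at the same two-sided 0.025.

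The primary outcome section (Hepatic injury and liver fat) comes closest to a definition: "Improvement in liver injury will be defined by reduction in non-invasive and biochemical markers of fibrosis and inflammation". It does not say whether one marker or all of them must fall. Nowhere does the article combine FibroScan and Fibrotest into a composite, require both, rank them, or split the 0.025 between them.

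**The concern.** A Bonferroni divisor has to count the tests that can each lead to a claim. Here the divisor counts labels. Whether that matters depends on a rule the article does not give.

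If a significant result on either FibroScan or Fibrotest is enough to declare that hepatic injury improved, three tests at 0.025 feed the primary claims and the hepatic-injury label spends nearly twice its share. If both are needed, two claims are tested and the divisor is correct.

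The gap also affects interpretation. Suppose FibroScan gives p = 0.02 and Fibrotest gives p = 0.40. The article as written cannot say whether the hepatic-injury outcome was met, and a rule chosen after unblinding could be chosen to suit the result.

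**Working it through.** **Inputs from the article.** Per-test level 0.025 two-sided; divisor 2; differences and SDs of 4.1 and 4.0 kPa (FibroScan), 0.08 and 0.056 (Fibrotest), 4.4 and 5.0 points (MRI); 80% power; equal allocation; 25 per group. **Assumed:** the correlations between test statistics, because the article gives none.

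**1. The plan's own figures.** 0.05/2 = 0.025. With n per group = 2(z₀.₉₈₇₅ + z₀.₈₀)²(SD/difference)², the multiplier is 2(2.2414 + 0.8416)² = 19.01.

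- FibroScan: 19.01 × (4.0/4.1)² = 18.1, so 19.
- Fibrotest: 19.01 × (0.056/0.08)² = 9.3, so 10.
- MRI: 19.01 × (5.0/4.4)² = 24.5, so 25.

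All three stated sizes reproduce by normal approximation (a t-test calculation gives 20, 11 and 26). Each measure was therefore planned as a separate test at 0.025.

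**2. Error if either fibrosis measure suffices.**

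- Upper bound: 3 × 0.025 = 7.5%.
- Independence: 1 − 0.975³ = 7.3%.
- Simulation of three correlated normal test statistics:

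| FibroScan–Fibrotest correlation | Each with MRI | At least one false claim |
|---|---|---|
| 0 | 0 | 7.3% |
| 0.3 | 0.2 | 7.1% |
| 0.5 | 0.2 | 7.0% |
| 0.7 | 0.4 | 6.4% |

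The hepatic-injury pair alone gives 1 − 0.975² = 4.9% at correlation 0 and 4.3% at 0.7, against a 2.5% share. With one common correlation among all three measures, the total is still 5.2% at 0.8 and drops to 4.4% at 0.9.

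**3. Error if both fibrosis measures are required.**

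- Independence, no true effects: 1 − (1 − 0.025)(1 − 0.025²) = 2.6%.
- Simulation over the same range of correlations: 2.6% to 3.2%.
- Whatever the true effects, a false hepatic-injury claim needs a false positive on a null fibrosis measure, so its rate is at most 0.025. Adding 0.025 for MRI gives at most 5%.

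**4. Power at 25 per group under each remedy.**

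*Both required at 0.025.* By t-test, power is 90.1% for FibroScan and 99.6% for Fibrotest. Joint power lies between 0.901 + 0.996 − 1 = 89.7% and 90.1%, whatever the correlation. MRI is untouched.

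*Holm at overall 0.05.* For MRI the expected z is (4.4/5.0) × √(25/2) = 3.111.

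| Level applied to MRI | Normal approximation | t-test |
|---|---|---|
| 0.025 (current) | Φ(3.111 − 2.241) = 80.8% | 78.5% |
| 0.05/3 = 0.0167 (Holm first step) | Φ(3.111 − 2.394) = 76.3% | 73.4% |

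The lower row is the worst case, in which MRI is the only true effect. Under the article's three assumed effects, the fibrosis measures are usually rejected first and MRI is then tested at 0.05. Simulated MRI power under Holm is then about 87% (normal approximation) or 85% (t-test), above the present figure.

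**The case against.** The strongest defence is that hepatic injury is one outcome with two measures, that a natural reading requires both, and that an article may leave the joint interpretation to an analysis plan not shown here. Part of this stands. Under the both-required reading the divisor of two is correct, and the absence of a fully specified decision rule would not by itself be a fault in an article. But the article does print a divisor and does power Fibrotest and FibroScan as separate tests at the full 0.025. Those statements fit together only under a rule that is not given.

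Positive correlation also reduces the excess. That is true and is included in the range above; but Bonferroni is used to avoid relying on an unknown correlation.

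Four stronger readings are tempting, and the article does not support them:

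- *The family-wise error is 7%.* This holds only if either fibrosis measure can carry the claim, which the article neither says nor excludes.
- *The plan breaks its stated 5%.* No overall 5% is written down. It is implied by 0.025 for two outcomes.
- *Naming inflammation in the primary outcome adds further tests.* It does not. The Statistical analyses section closes the primary list at three measures, the Sample size calculation section powers the same three, and inflammatory markers sit under secondary outcomes. The word is a labelling mismatch and contributes nothing to the figures here.
- *Any repair costs MRI power.* Requiring both costs MRI nothing. Holm lowers MRI power only if the fibrosis effects fail to appear.

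**Conclusion.** The point holds in conditional form. The divisor of two does not match three separately powered tests unless FibroScan and Fibrotest are joined by a rule, and the article has none.

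If either suffices, the error exceeds the implied 5% by about 1.4 to 2.3 percentage points, on the assumed correlations of 0 to 0.7 between the fibrosis measures and 0 to 0.4 with MRI. If both are required, there is no excess. The size is moderate, but it bears on the trial's primary claims, and the article does not settle which case applies.

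**What to change.** Choose one rule and record it before unblinding.

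**(a) Keep 0.025.** State that hepatic injury is claimed only if FibroScan and Fibrotest both reach two-sided 0.025, with MRI liver fat tested separately at 0.025. The count of two is then correct. Cost: one sentence. MRI power is unchanged, and joint power for the pair is about 90% at 25 per group on the article's assumptions.

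**(b) Use Holm.** Test the three measures at overall two-sided 0.05 (steps 0.0167, 0.025, 0.05), state the overall level, and report each measure as its own claim. Cost: one sentence and a restated power paragraph. That paragraph should give the MRI worst case (73% by t-test, 76% by normal approximation, at 25 per group) beside the figure under the three assumed effects. Guaranteeing 80% for MRI at 0.0167 would need 28 evaluable per group by normal approximation or 29 by t-test.

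Neither option needs new data, and (a) needs no extra participants. Separately, align the primary outcome label in the abstract and the primary outcome section with the three listed measures.

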## Discussion

The prevalence of NAFLD continues to increase worldwide in parallel with obesity and insulin resistance. Despite a multiplicity of factors working in concert to promote the development and progression of the disease, there is sufficient evidence linking NAFLD with dysbiosis of the gut microbiota to warrant an intervention aimed at prebiotic-mediated manipulation of the gut microbiota. Further support for the immediate need for this trial comes from the realization that there are few approved treatment options for NAFLD patients. While the standard of care for patients with NAFLD focuses on weight loss through diet and exercise, the difficulty in achieving and maintaining weight loss is well documented. Given that dietary prebiotic intake is associated with subjective improvements in satiety, there is the added potential for prebiotics to improve adherence to the weight loss intervention. Although approved therapies for NAFLD are still lacking, capitalizing on the gut microbiota–liver axis may provide new therapeutic targets in future.

The planned double blind, randomized clinical trial will determine whether adding prebiotic to a 6-month weight loss intervention will augment improvements in hepatic steatosis and fibrosis attributed to weight loss alone in the placebo group receiving an identical weight loss intervention but without supplementation. The exploration into the mechanisms of action is critically important in advancing treatment options for NAFLD and this study will specifically address *de novo* lipogenesis and metagenomic analysis of gut microbiota and their associated metabolic by-products (i.e. VOCs). Ultimately this clinical trial will advance our understanding of the magnitude to which NAFLD can be treated with a dietary intervention aimed at modulating the gut microbiota.

The proposed study design using daily packets to be consumed with water prior to a meal is feasible as indicated by our previous research [72] and is similar to soluble fiber supplements already on the market. More promising, however, is the versatility of prebiotics. Foods supplemented with prebiotics are already in production because the physical properties and sweet taste allows manufactures to decrease the caloric value while maintaining the palatability and texture of the food [111]. This ease of incorporation is important given the surge in interest in manipulation of the gut microbiota to prevent or treat conditions such as obesity and inflammatory bowel disease. While other options including fecal transplantation and antimicrobial-based interventions are being tested as viable means to manipulate the gut microbiota, targeted dietary interventions such as prebiotics or probiotics are easy to administer and for the most part have good safety and tolerance records [112]. While both prebiotics and probiotics are promising means to manipulate the gut microbiota, unlike prebiotics, probiotics must remain viable during storage and also be capable of surviving the harsh intestinal environment of the host in order to exert their beneficial effects [113]. Additionally, given the well-established health promoting properties of prebiotics and their tolerability, they could be used not only as a treatment but also as a prophylactic.

This trial will assess the ability of a prebiotic to improve overall health in a group at high-risk for a host of metabolic diseases. Improvement in liver health is expected, as are improvements in other predictors of the metabolic syndrome. Ultimately, the research will provide clinical evidence for a potential low-risk treatment option for NAFLD patients. Should the prebiotic intervention prove beneficial, it could have a significant impact on the ability of health professionals to recommend evidence-based targeted dietary interventions for managing NAFLD.

